#### Strategies to improve adherence to interventions {11c}

OptiMAT will send daily reminders for participants to log their daily self-monitoring assessment. Additionally, study staff will review mean OptiMAT use (percent days per month) at each of the participants’ monthly follow-up visits and provide strategies to maintain consistent OptiMAT use.

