##### Secondary outcome

The RCT will have several secondary outcome variables: self-reported days of opioid misuse, time to opioid lapse, and time to treatment discontinuation. Self-reported days of opioid misuse will be assessed using the TimeLine Follow-Back Calendar (TLFB) [23]. The TLFB is a calendar that provides cues (such as holidays) to prompt participants to recall days of opioid misuse over the past month. TLFB will be administered at study enrollment (baseline) and monthly by phone to record opioid misuse over the 6-month RCT. TLFB offers more granularity for days-per-month of opioid misuse than a quantitative urinalysis test but is subject to misreporting. Days of opioid misuse will be collected monthly in the 6-month study.

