#### Data management {19}

These data will be stored in patients’ electronic medical records (EMRs). All other surveys and instruments will be administered by research staff using REDCap (Research Electronic Data Capture) database, a secure web-based database for collecting and storing survey-based research data [27]. REDCap includes logic to detect incorrect data entry such as range check for data values. Research staff will manually enter urinalysis results from EMRs into REDCap with double data entry. For privacy and confidentiality, the REDCap database will store information by coded study ID without PHI linkages.

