### Statistical methods

#### Statistical methods for primary and secondary outcomes {20a}

##### Analyses of primary and secondary outcomes

The adequacy of randomization will be assessed by comparing baseline variables with known prognostic importance between the MOUD+OptiMAT and MOUD-only study arms. These baseline variables include demographic variables (age, sex, etc.) and clinical variables (Suboxone dose at initiation, initiating MOUD in a residential setting prior to initiating outpatient MOUD, etc.). An imbalance between the study arms is suspected if the proportion of variables with significant differences (*p* < 0.05) exceeds 5%. We will then run the statistical models below with and without those variables identified as being associated with imbalance between the groups included and compare the results. If the results from both approaches are similar, we will use the models without those variables included. Otherwise, we will adjust those variables in the models.

We will next assess missing data. If the percentage of missing data is large, multiple imputation will be performed if the missing pattern is missing at random. If the pattern is not missing at random (NMAR), other methods like Bayesian models will be used. Distributions of outcome variables will also be assessed using appropriate tests and visual graphs. Linearity between continuous covariates and outcomes will be checked and other functional forms of the covariates will be used if the linear relationships are not shown.

General linear or generalized linear models (GLMs) will be used to examine associations between study arms and primary outcome (percent negative urinalysis tests) at the 6-month endpoint depending on whether the outcome is normally distributed or not. The model will include the indicator variable for study arm (MAT+OptiMAT vs. MAT-only) and the three stratification variables used for randomization (Site, Chronic Pain, and comorbid Alcohol or Marijuana Use) only first. Then, the model will be run again with any additional covariates that were identified as being unbalanced between the study arms, and results will be compared.

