For the secondary outcome of days-per-month of opioid misuse over the course of the 6-month study period, we will use generalized linear mixed models (GLMMs) to account for multiple records within each participant with Poisson or negative binomial distribution specified (as the outcome is probably skewed). GLMM will allow us to examine if overall days-per-month of opioid misuse varies between study arms and if this difference varies by study month. The models will include the indicator variable for MAT+OptiMAT vs. MAT-only, time with values 1 to 6 representing each of the six outcome variables measured monthly, time by study arm indicator interaction, strata variables and baseline days of misuse without and with additional covariates identified above added. The results from both models will then be compared.

If the percentage of missing data is deemed large and missing is not at random (MNAR) or if the planned sample size is not met, we will then use Bayesian methods for the analyses as Bayesian methods are more robust for small samples and can handle MNAR data by modeling the missing values. Posterior mean parameter ratios and posterior probabilities of the mean parameter ratios in the log scale being positive will be calculated. Bayesian models will include the models for outcomes and the models for indicator variables for missing values. The same variables as described in the previous paragraphs will be included. For the secondary outcome of days-per-month of opioid misuse, models will be fit separately for days of opioid misuse at each month with corresponding models fitted for the missing outcomes. Non-informative priors will be specified for all parameters. Convergence diagnostics tests such as Geweke, Raftery-Lewis, Heidelberger-Welch, Effective Sample Size, and posterior autocorrelations will be used to evaluate Markov chain convergence. Visual trace plots will also be used to aid evaluation of Markov chain convergence.

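### The Bayesian missing-data models for monthly self-reported misuse name no post-baseline information, although same-month urinalysis and attendance are recorded in both arms

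*Protocol article*

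**What the plan says.** The outcome is collected by telephone: "TLFB will be administered at study enrollment (baseline) and monthly by phone to record opioid misuse over the 6-month RCT" (Secondary outcome). The planned GLMM contains arm, month and "time by study arm indicator interaction, strata variables and baseline days of misuse without and with additional covariates identified above added" (Analyses of primary and secondary outcomes).

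The same section gives two routes for large amounts of missing data:

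- **Missing at random:** "multiple imputation will be performed if the missing pattern is missing at random". The imputation variables are not listed, and section {20c} repeats the rule without adding any.
- **Not at random, or planned sample size not met:** "Bayesian models will include the models for outcomes and the models for indicator variables for missing values", with non-informative priors. Here a variable list is fixed: "The same variables as described in the previous paragraphs will be included". For this outcome, "models will be fit separately for days of opioid misuse at each month with corresponding models fitted for the missing outcomes".

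Other sections show what the trial records apart from the phone call. Urine is tested at each clinical visit (Primary outcome). Missed urinalysis tests are documented ({11b}). Treatment discontinuation is derived from consecutive missed appointments ({18a}). For the database, "Research staff will manually enter urinalysis results from EMRs into REDCap with double data entry" ({19}).

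**The concern.** A participant who is using opioids may be harder to reach by phone, so the lost months may be the heavier ones. The listed variables are all baseline quantities apart from the month index, and that index drops out once each month is fitted alone. They cannot tell a lost month of abstinence from a lost month of heavy use. The clinic's tests and attendance for the same month often can, and the protocol itself treats absence as informative, since its primary outcome scores a missed test as positive.

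At stake is the arm comparison on this secondary outcome. If heavier months are lost more often in MOUD-only, that arm looks better than it was and a benefit of the app is understated. The reverse pattern overstates it.

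**Working it through.** **No figure in the plan to reproduce.** The protocol gives no rate of missed calls. Its only attrition figure, 20% drop-out, belongs to the sample size for the primary comparison.

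**What the listed variables can do.** Let Y be the days of misuse in a month, M the missing indicator, X the listed variables, and A the same-month urinalysis, missed tests and treatment status. The text does not say whether Y enters the model for M.

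1. If it does not, P(M | Y, X) = P(M | X). Missing days are then filled from the observed days at the same X. This is missing at random given baseline, not a model for MNAR data.
2. If it does, the coefficient of Y in the model for M concerns values never seen. It is identified only through the assumed shape of the distribution, and non-informative priors add nothing.
3. Adding A to the model for M alone does not help. Without Y in that model, it separates from the outcome model and the imputed days do not change. With Y in it, the model takes Y and A as independent given X, which is wrong because both reflect drug use. A has to be tied to Y.

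**Size, one-month simulation.** All parameters are assumptions. There were 400,000 participants per scenario. Days were negative binomial, capped at 30, with a control mean of about 2.7. Other settings:

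- Attendance: logit = 2.0 − 0.12Y.
- A positive test, if attending: probability 1 − exp(−0.25Y).
- Loss A: logit = base + g(1.5 × positive test + 2.0 × non-attendance).
- Loss B: logit = base + g × 0.2Y.

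The baseline-only analysis regresses observed days on arm and baseline days. The other analysis first fills missing days from arm, baseline days, urinalysis and attendance. Entries are rate ratios, app over control.

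| Loss | Pattern | Missing, control/app | Full data | Baseline only | With auxiliaries |
|---|---|---|---|---|---|
| A | same in both arms | 25%/25% | 1.006 | 1.010 | 1.012 |
| A | higher level in control | 34%/18% | 0.998 | 1.114 | 1.001 |
| A | use-driven in control only | 25%/12% | 0.989 | 1.151 | 0.987 |
| A | use-driven in app only | 12%/25% | 1.001 | 0.856 | 0.999 |
| B | same in both arms | 21%/21% | 1.001 | 0.997 | 0.999 |
| B | higher level in control | 29%/14% | 0.993 | 1.144 | 1.104 |
| B | use-driven in control only | 21%/12% | 1.003 | 1.369 | 1.281 |
| B | use-driven in app only | 12%/21% | 1.001 | 0.731 | 0.781 |

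With a true ratio of 0.80, the three differential patterns under A gave 0.911, 0.932 and 0.691 with baseline variables only, and 0.814, 0.799 and 0.800 with auxiliaries. Under A with the same mechanism in both arms, the baseline-only result was 0.807 against 0.803 in full data. Under B it was 0.848 against 0.795, a small bias toward no effect.

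Under B the auxiliaries removed only part of the bias. For the higher level in control, (1.144 − 1.104)/(1.144 − 0.993) = 0.040/0.151, about 26%. For use-driven loss in the app arm only, (0.781 − 0.731)/(1.001 − 0.731) = 0.050/0.270, about 19%.

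**Size, six-month simulation.** This used 16,000 people, a planted ratio of 0.65 and a negative binomial random-intercept GLMM.

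| Loss depends on | Missing, control/app | Full data | Observed months | Imputed, model variables | Imputed, with auxiliaries |
|---|---|---|---|---|---|
| urinalysis and missed tests | 24%/13% | 0.67 | 0.77 | 0.77 | 0.67 |
| unseen days | 31%/14% | 0.67 | 0.84 | 0.83 | 0.73 |

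In the second row the auxiliaries removed (0.84 − 0.73)/(0.84 − 0.67) = 0.11/0.17, about 65%. With the same dependence in both arms the result was 0.66 against 0.67.

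**Limit of both simulations.** Neither fits the Bayesian joint model. The baseline-only regression approximates reading 1, where the indicator model carries no information on the missing days. It says nothing about what reading 2 would give.

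**The case against.** Four objections carry weight.

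- **Scope.** A reader might infer that all the missing-data models, multiple imputation included, are confined to the outcome-model variables. The documents do not support that. The fixed list stands in the Bayesian paragraph, and the imputation variables are simply not given, which a full analysis plan may settle. Nor does the sentence say that nothing else may enter. What stands is that the one list given names no post-baseline variable.
- **Differential contact.** A reader might also infer that contact does differ by arm, because "study staff will review mean OptiMAT use (percent days per month" at monthly follow-up visits and only the app arm has a month-2 interview. The review is an item within those monthly visits and is not shown to be an extra contact. The TLFB calls are not restricted to one arm, and the retention contacts in {18b} cover all participants. A difference is possible but not shown, and the missingness gaps used above are assumed.
- **Built-in recovery.** Full recovery under loss A follows from making loss depend on exactly the variables that are added. Loss B is closer to the worry that users are harder to reach, and there the gain is partial.
- **Reach.** This is one secondary outcome. The primary outcome rests on urinalysis and counts missed tests as positive.

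These objections limit the claim. They leave untouched the point that relevant recorded information is not used in the route meant for informative loss.

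**Conclusion.** The point holds for the Bayesian route and this secondary outcome. As listed, the models are either missing at random given baseline, or identified only by distributional form under non-informative priors, while informative same-month data are left out.

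Bias in the arm comparison needs loss that follows drug use or attendance and that differs by arm. Under the assumed differential patterns tabulated, a true ratio of 1.00 moved to 1.11 to 1.15, or to 0.86, when loss followed urinalysis and attendance. It moved to between 1.14 and 1.37, or to 0.73, when loss followed the unseen days. With the same mechanism in both arms the bias was near zero in all but one setting, where 0.80 became 0.85. The direction cannot be told in advance. The documents do not support saying that the comparison will be biased, and the primary outcome and sample size are unaffected. This is a cheap improvement.

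**What to change.** In the section on analyses of primary and secondary outcomes, state that missing monthly days will be imputed within arm. Name as auxiliary variables that month's proportion of urinalyses positive for opioid misuse, the number of missed tests or appointments, treatment status, and the other months' reports. Then fit the planned GLMM to the imputed data without the clinic auxiliaries as covariates, since they arise after randomisation.

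If the Bayesian route is kept, model the auxiliaries jointly with the days of misuse, not in the missingness model alone. Keep an MNAR sensitivity analysis, because the auxiliaries reduce but do not remove bias when loss depends on the unseen days. Settle the wording before outcome data are seen.

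The cost is analysis text and a larger imputation model. No new data collection is needed: urinalysis results go into REDCap, missed tests are needed for the primary outcome, and missed appointments come from clinical records for time to discontinuation. The gain is small for months after a participant has left the clinic, when only treatment status is still known.

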#### Methods for additional analyses (e.g., subgroup analyses) {20b}

##### Subanalyses of OptiMAT usage patterns predicting outcome

Subanalyses will evaluate if usage of specific OptiMAT features predict treatment outcomes. Missing data and data normality will be assessed as described above, with methods adjusted accordingly. First, GLMM will evaluate if concurrent opioid misuse can be predicted from daily ratings of opioid craving, opioid withdrawal, stress, anger, sadness, alcohol use, and/or marijuana use. GLMM will also evaluate if these variables can predict subsequent opioid misuse (within the next week). Second, GLMM analysis of GPS data will evaluate if opioid misuse can be acutely predicted by entering hotspots, duration of time spent in hotspots, or craving ratings while in hotspots.

Third, qualitative interviews conducted at the 2-month endpoint will evaluate which OptiMAT features (e.g., the Tip Bank, Graphs of daily ratings, sobriety resources) participants report as most beneficial and which of these features most reliably predict 6-month outcome. We will use established procedures to enhance the trustworthiness of our analysis, including triangulation of data generated from multiple methods and participants, team de-briefings, prolonged engagement with study site, and development of an audit trail. Interviews will be digitally recorded, de-identified, transcribed, and uploaded to MAXQDA qualitative data analytic software (http://maxqda.com/). We will conduct conventional content analyses to create preliminary a priori and emergent themes within which to sort participant quotes [28]. Two coders will code interviews to enhance rigor in analysis. First, we will develop a preliminary codebook consisting of top and sub-level codes after reading 2–3 transcripts [29]. Then, we will independently code 10% of transcripts and compare results; through discussion, we will refine the codebook. Next, we will independently code a different 10% of transcripts and compare results with interrater reliability. If interrater reliability is acceptable, with consensus, we will divide and independently code remaining transcripts to determine final themes. To further develop the thematic templates once interviewing has begun, coding will occur in an iterative fashion, with the templates being expanded and refined. We will also employ a quick and comprehensive qualitative analysis strategy, termed the rigorous and accelerated data reduction (RADaR) technique [30], which involves using tables and spreadsheets from general-purpose word-processing software to develop all-inclusive data tables. These tables undergo several revisions, called data reduction, which produces more concise data tables. The RADaR technique: converts raw, textual data in to a more manageable and user-friendly format; is rigorous because of the systematic analysis that occurs at each step; and is accelerated because the time required to review and reduce each phase of the data table becomes shorter as the user produces more condensed and concise presentations of the textual data. Ultimately, we will produce “final” templates that will be applied to all of the interview data using MAXQDA qualitative coding software [31]. Once the templates have been applied to the transcripts, we will perform interpretive analyses to connect and contextualize the themes/recommendations and map out relationships across themes/recommendations.

#### Methods in analysis to handle protocol non-adherence and any statistical methods to handle missing data {20c}

We will assess missing data as described in {20}. If the percentage of missing data is large, multiple imputation will be performed if the missing pattern is missing at random. If the pattern is not missing at random (NMAR), other methods like Bayesian models will be used. Distributions of outcome variables will also be assessed using appropriate tests and visual graphs. Linearity between continuous covariates and outcomes will be checked and other functional forms of the covariates will be used if the linear relationships are not shown.

#### Plans to give access to the full protocol, participant-level data, and statistical code {31c}

To promote study transparency and open science, published findings will include links to deidentified BIDS-compliant datasets and statistical code used for analyses.

### Oversight and monitoring

#### Composition of the coordinating center and trial steering committee {5d}

The principal investigator [name] will meet as needed (at least weekly) with study staff to review study progress. [name] will work with study staff to troubleshoot and resolve issues relating to study recruitment and day-to-day conduct. [name] meets weekly with Drs. [name] and [name] (co-creators of the OptiMAT smartphone app) and monthly with all study co-investigators and consultant to discuss study progress.

#### Adverse event reporting and harms {22}

Adverse events (AE), serious adverse events (SAE), and unanticipated problems involving risks to subjects or others (UPIRSO) will be reported per UAMS IRB policy. Briefly, staff members will complete an initial AE report upon learning that an AE has occurred. The PI [name] will review individual AE reports briefly and discuss these reports at a weekly meeting with co-investigators Drs. [name] and [name]. Drs. [name], [name], and [name] will determine if an AE meets the criteria for a SAE or UPIRSO. UAMS IRB policy states that an AE should be considered an UPIRSO if it was unanticipated, related to the research, and involves some increased risk to the subject. The PI will report AEs annually to the IRB at continuing review and to NIDA during the annual progress report. The PI will report SAEs and UPIRSOs to the IRB and NIDA PO within 10 days of learning of the event. UAMS IRB and/or NIDA may request modification of RCT procedures in response to the event. The PI and study team will follow all AEs to satisfactory resolution by the UAMS IRB. This may include withdrawing a subject if the investigative team determines that doing so is the best decision to protect the participant’s safety. Participants withdrawn from the RCT due to an SAE will have appropriate follow-up medical monitoring, which will be reported to the UAMS IRB and NIDA.

#### Frequency and plans for auditing trial conduct {23}

Per UAMS policy, study data will be available to the UAMS Office of Research Compliance (ORC) at all times for review. ORC may conduct audits of study procedures. Findings from these audits will be reported to the UAMS IRB for review of study safety and protocol deviations. The IRB will communicate audit-related decisions to the PI in a timely manner. In the IRB takes an action that impacts the day-to-day operations of the trial (e.g., suspends recruitment, halts the RCT), the PI will report those actions to the NIDA program officer within 3 business days of receipt, consistent with NIDA policy.

#### Plans for communicating important protocol amendments to relevant parties (e.g., trial participants, ethical committees) {25}

Per UAMS policy, the IRB will review all proposed protocol modifications. IRB reserves the right to deny unjustified protocol modifications. If the IRB determines that a protocol modification or DSMB committee report impacts the study risk-benefit ratio, the IRB may require that the modification or DSMB report be provided in writing to current and/or former study participants. Protocol modifications will be updated as they occur in ClinicalTrials.gov and reported annually to NIDA via continuing review.

#### Dissemination plans {31a}

Trial results will primarily be disseminated through peer-reviewed publications. Trial results may also be communicated via media interviews, news releases, or conference proceedings.

## Discussion

We have described our planned protocol for a randomized controlled trial evaluating adjunctive use of smartphone app OptiMAT to improve 6-month outcomes for patients receiving MAT for OUD. We believe that OptiMAT’s use of daily monitoring, personalized feedback, and GPS-driven just-in-time intervention will reduce opioid misuse during this 6-month trial.

Our trial design includes several best practices for RCT methodology, including stratification of study arm assignment by key study variables suspected to influence outcome (comorbid pain interference and comorbid use of alcohol or marijuana); reliance on the Treatment Effectiveness Score for primary outcome of negative urinalysis test; data safety monitoring; and inclusion of secondary outcomes for participants who discontinue MOUD treatment. We acknowledge that study confounds may still arise despite these best practices and provide an adaptable statistical plan that can be tailored to the specific data properties of the resulting dataset (e.g., adjusting for non-normal distributions and patterns of missing data).

We additionally provide subanalyses for evaluating the OptiMAT features and usage patterns that best predict 6-month outcomes. These subanalyses seek to identify the mechanisms by which app-based interventions promote positive outcomes, and thus identify the critical components for future app interventions.

